### Statistical Analysis

SPSS (version 25; IBM Corp) [80] will be used to analyze the quantitative data from the surveys. Surveys with more than 50% missing responses will not be included in the data analysis. There will be no missing data imputation, and the analysis of the included survey responses and results will be based on completed survey data. Descriptive statistics for demographic, mental health literacy, clinical, and burnout-related variables will be provided. A 2-tailed *P*≤.05 will be used to determine statistical significance for all analyses, and descriptive characteristics will be presented as percentages and numbers. A chi-square test and logistic regression analysis will be used to separately identify demographic, clinical, and work-related correlates of anxiety, depression, stress, low resilience, and burnout for elementary and high school teachers. Significant and borderline significant variables from the chi-square analysis would be used to develop multivariable binary logistic regression models to predict the adjusted odds of outcomes for the exposure of interest and each potential correlate. The impact of the email supportive messaging program in reducing moderate to high anxiety, moderate to high depression, moderate to high stress, burnout, and improving resilience among subscribers will be evaluated by comparing the mean changes in these parameters from baseline to 6 weeks, 3 months to 6 months, and 12 months using the paired *t* test. To assess the effects of the intervention against a control group, we will choose a defined period of 3 months during the study period (for instance, the beginning of January 2023 to the end of March 2023) and compare the prevalence and mean scores on standardized scales for stress, anxiety, burnout, and depression at 6 weeks for subscribers who have received the daily supportive SMS text messages for 6 weeks (the intervention group) to the baseline prevalence and mean scores on the same scales for new subscribers during the period (the control group).

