### Data Collection

Quantitative data will be collected using web-based questionnaires through the ResilienceNHope secure platform for managing web-based surveys and databases [57]. The web-based questionnaires will be designed to collect demographic and work-related variables and assess mental health literacy and clinical variables, including stress, burnout, anxiety, depression, and resilience [59]. The web-based surveys will be distributed to subscribers on enrollment at 6 weeks, 3 months, 6 months, and 12 months. The follow-up surveys will also include questions assessing subscriber experience and satisfaction with the Wellness4Teachers email messaging program.

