### Outcomes and Measures

Validated screening scales for self-reported symptoms will be used to assess clinical outcomes. These include the Mental Health Literacy Scale [69], the Generalized Anxiety Disorder 7-item (GAD-7) Scale (a GAD-7 score of ≥10 indicates moderate to high anxiety) [70], the Perceived Stress Scale (PSS-10) (a PSS-10 score of ≥10 indicates likely moderate to high stress) [71], the Brief Resilience Scale (BRS; BRS mean scores ranging from 1.00 to 2.99 indicate low resilience, scores from 3.00 to 4.30 suggest normal resilience, and mean scores from 4.31 to 5.00 suggest high resilience) [72,73], and the Patient Health Questionnaire-9 (PHQ-9; a score of ≥10 indicates moderate to high depression) [74]. Burnout will be assessed using the Maslach Burnout Inventory (MBI), specifically the MBI-Educators Survey, for use with educators [75,76]. An exploratory outcome will be to evaluate the acceptance of the Wellness4Teachers program by teachers in Zambia, which can be measured by the proportion of the target population (teachers in Livingstone, Lusaka, Kasama, and Solwezi) who subscribe to the program. Primary outcomes for this study will be changes in mental health literacy and the prevalence of moderate to high stress, burnout, moderate to high anxiety, moderate to high depression, and low resilience from baseline to 6 weeks, 3 months, 6 months, and 12 months among the subscribers of the Wellness4Teachers Zambia program. Secondary outcomes include the mean score on the Mental Health Literacy Scale and the prevalence of moderate to high stress, burnout, moderate to high anxiety, moderate to high depression, and low resilience at baseline in subscribers of the Wellness4Teachers email messaging program. Other secondary outcome measures will include changes in mean scores on the PSS-10, MBI, GAD-7, PHQ-9, and BRS. In addition, sociodemographic factors, work-related factors, and mental health literacy correlate with moderate to high stress, burnout, moderate to high anxiety, moderate to high depression, and low resilience at baseline among subscribers of the Wellness4Teachers program.

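### Completeness is judged on the whole survey, but the anxiety, stress and depression endpoints are single-scale scores, so the rule can discard complete scales and leaves the scoring of incomplete ones unsettled

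*Protocol article*

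**What the plan says.** Two consecutive sentences in the Statistical Analysis section govern missing answers. The first is a screen on the survey: "Surveys with more than 50% missing responses will not be included in the data analysis". The second reads "There will be no missing data imputation, and the analysis of the included survey responses and results will be based on completed survey data".

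The endpoints are defined in Outcomes and Measures, scale by scale:

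- Anxiety: "a GAD-7 score of ≥10 indicates moderate to high anxiety".
- Stress: "a PSS-10 score of ≥10 indicates likely moderate to high stress".
- Depression, on the PHQ-9: "a score of ≥10 indicates moderate to high depression".
- Resilience uses an item mean rather than a total: "BRS mean scores ranging from 1.00 to 2.99 indicate low resilience".
- For burnout the instrument is named, but no cut-off is given.

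Changes in these prevalences from baseline to each follow-up, together with mental health literacy, are primary: "Primary outcomes for this study will be changes in mental health literacy and the prevalence of moderate to high stress, burnout". Baseline prevalence is a secondary outcome. On the content of the surveys, Data Collection adds that "The follow-up surveys will also include questions assessing subscriber experience and satisfaction with the Wellness4Teachers email messaging program".

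**The concern.** A completeness rule should act on the unit that is analysed. Here the unit of the rule is the questionnaire and the unit of the endpoint is one instrument, so the rule can err in both directions.

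It can remove valid data, because a teacher's complete depression scale is lost if the rest of the form is mostly blank. It can also admit incomplete data, because a survey with up to half of its answers missing passes the screen and may contain a partly answered or empty scale. The second sentence does not settle what then happens. "Completed" could mean a fully completed survey (which makes the 50% threshold redundant), a complete scale within a retained survey, or a submitted survey that passed the screen.

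At stake are three of the primary prevalence outcomes and their baseline estimates. A partial total compared with a cut-off meant for a full scale is too low, so cases would be missed.

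**Working it through.** No figure in the article depends on this rule, so there is none to reproduce. The check has four steps.

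**1. Can the rule discard complete scales?** From the instrument names, GAD-7, PHQ-9 and PSS-10 have 7 + 9 + 10 = 26 items. Let the whole survey have T items, and let a teacher answer exactly these 26. The survey is excluded if (T − 26)/T > 0.5, that is, if T > 52. The survey also carries literacy, burnout, resilience, demographic and work-related questions. T is not stated, so how often this happens cannot be calculated. No assumption about scoring blanks is needed here.

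**2. Can the rule retain incomplete scales?** Yes. An entirely blank GAD-7 is 7/26 = 27% of these three scales, and four blank GAD-7 items are 4/26 = 15%. Both shares are smaller in the full survey. If all else is answered, both surveys stay in.

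**3. What would partial sums do?** This step assumes that blanks add nothing to the total, which the article does not say, and that GAD-7 and PHQ-9 items score 0 to 3 and PSS-10 items 0 to 4, which it does not print. The highest attainable GAD-7 total with k blanks is 3 × (7 − k): 12 with three blanks and 9 with four. With four blanks no respondent can reach 10.

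An illustrative simulation (latent inter-item correlation 0.6, blanks at random) gives the share of true cases that fall below 10:

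| Scale (prevalence set at) | 1 blank | 2 blanks | 3 blanks |
|---|---|---|---|
| GAD-7 (38.0%) | 22% | 47% | 76% |
| PHQ-9 (35.5%) | 14% | 31% | 49% |
| PSS-10 (80.4%) | 4% | 10% | 18% |

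A second simulation of a nine-item scale, with loading 0.75 and prevalence 31.5%, agrees for the PHQ-9: 69.5% of cases are retained with two blanks, so 30.5% are lost.

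**4. Effect on change.** Let L be the share of cases lost, and q0 and q1 the shares of surveys with gaps at baseline and follow-up. With stable true prevalence, observed follow-up prevalence divided by observed baseline prevalence is (1 − q1·L)/(1 − q0·L).

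- Equal gaps (q0 = q1): the ratio is 1, so there is no false change.
- Gaps only at follow-up, GAD-7, q1 from 5% to 30%: with one blank the false relative fall is 0.05 × 0.217 = 1.1% to 0.30 × 0.217 = 6.5%. With three blanks it is 0.05 × 0.758 = 3.8% to 0.30 × 0.758 = 22.7%. The hypothesised reduction is 20%.
- More gaps at baseline, three blanks, q0 = 30% and q1 = 5%: 0.9621/0.7726 = 1.25, a false rise that works against the programme.

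Equal gaps would still lower baseline prevalence. With 20% of surveys affected, GAD-7 prevalence falls by 0.20 × (0.380 − 0.298) = 1.6 points with one blank and by 0.20 × (0.380 − 0.092) = 5.8 points with three. The planned margin of error is 3%.

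All values of q and k are assumptions. The article gives no item-missingness rates.

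**The case against.** The strongest reply is that the plan may already be safe. Counting a blank as 0 is a form of imputation, and the plan excludes imputation. A natural complete-case reading is that a survey first passes the 50% screen and each analysis then uses respondents with complete data for it. On that reading misclassification from this source is zero, and the cost is a smaller sample and possible selection. This stands: a reader might infer that incomplete totals will be set against the cut-offs, but the text does not say so.

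A reader might go further and infer that teachers will be misclassified as recovered. That needs both partial sums and more gaps at follow-up. The article gives no evidence for the second: it adds questions to the follow-up surveys, but states no lengths and does not say whether the demographic questions are repeated. It is also limited to three scales. The BRS uses a mean, the MBI has no stated cut-off, and blanks summed as 0 on the literacy scale would hide benefit, not create it. The larger simulated effects need a complete baseline and several blanks in up to 30% of follow-up surveys, which is an extreme combination.

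It can also be said that item-level scoring belongs in the full protocol or SAP. That is fair for a rule that is merely absent. Here the article does state a rule, at the wrong unit, and does not reconcile it with the next sentence. Even the complete-case reading leaves the loss of complete scales in mostly blank surveys.

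**Conclusion.** The point holds in limited form. The 50% rule does not match the endpoints it serves. It discards fully answered scales when more than half of the survey is blank, and it retains incomplete scales without fixing their treatment. Because the extra follow-up questions enter the denominator, the same answers on a scale need not be treated alike at every visit.

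A downward bias on GAD-7, PHQ-9 and PSS-10 is a possibility, conditional on summing only the answered items. Apparent improvement also requires more gaps at follow-up than at baseline. The simulated figures show direction and order of magnitude under assumed missingness and item correlation; the actual size cannot be derived from the document. This is an inexpensive improvement to a stated rule, and it does not show that the planned results would be biased.

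**What to change.** Replace the survey-level 50% rule with one per-instrument rule, applied identically at baseline, 6 weeks, 3 months, 6 months and 12 months:

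- Score an instrument only if it is complete; otherwise set that instrument to missing.
- Never sum blanks as 0.
- Keep the teacher's other scorable instruments, whatever share of the survey is blank.

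If partly answered scales are to be used, state an exception to the ban on imputation: score when at least 80% of the items are answered, pro-rated by the mean of the answered items. That allows one blank on the GAD-7 (6/7 = 86%), one on the PHQ-9 (8/9 = 89%) and two on the PSS-10 (8/10). In the first simulation, pro-rating at these limits gave prevalences of 35.8% against 38.0%, 35.3% against 35.5%, and 80.5% against 80.4%. It is close for two scales and slightly low for the GAD-7, where a raw sum gave 29.8%. The complete-scale version keeps the plan's choice of no imputation.

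The cost is one sentence in the analysis section. The downside is that a few partly answered scales are dropped or pro-rated.

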### Participants’ Recruitment and Subscription

Subscription to the Wellness4Teachers email messaging program will be initiated by individual teachers accepting an invitation to subscribe from the Lusaka Apex Medical University’s organizational account on the ResilienceNHope web-based application. The local principal investigator (CC) will work with the Zambian Ministry of Education, the Lusaka Teachers Association, district school boards, and heads of elementary and high schools to invite teachers to join the Wellness4Teachers email messaging program. Participants will be eligible for inclusion if they are school teachers and residents of Livingstone, Lusaka, Kasama, or Solwezi. Subscribers can unsubscribe from the program at any time by clicking the unsubscribe link associated with the messages. Based on the 10% dropout rate recorded for the Text4Hope program [51,52], the anticipated dropout rate for the email messaging program will be less than 15% [54].

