### Sample Size Estimation

With the total teacher population in Lusaka, Livingstone, Kasama, and Solwezi of about 30,561 [66], using a web-based script [77], it is projected that the sample size needed for our prevalence estimates with 95% confidence and a 3% margin of error for moderate to high stress, burnout, moderate to high anxiety, moderate to high depression, and low resilience among teachers in Livingstone, Lusaka, Kasama, and Solwezi will be 993. Based on the maximum survey completion rate attained for the Text4Hope and Text4Mood programs in Alberta of 20% [50,78,79], to achieve an estimated 993 completed surveys at baseline, it is planned to enroll at least 4965 teachers in the Wellness4Teachers email supportive and mental health literacy messaging program within 12 months.

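### Change from baseline is tested only in teachers who answered both surveys, at an expected response of 20% or less; a repeated-measures model on all surveys is the better choice

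*Protocol article*

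**What the plan says.** All references are to the protocol article.

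- **Waves and outcomes.** Data Collection: "The web-based surveys will be distributed to subscribers on enrollment at 6 weeks, 3 months, 6 months, and 12 months". Outcomes and Measures: "Primary outcomes for this study will be changes in mental health literacy and the prevalence of moderate to high stress, burnout", followed by anxiety, depression and low resilience, each from baseline to the four follow-ups.
- **Test.** Statistical Analysis names a t test on pairs for the programme's impact, in these words: "comparing the mean changes in these parameters from baseline to 6 weeks, 3 months to 6 months, and 12 months using the paired". A two-sided 0.05 level "will be used to determine statistical significance for all analyses".
- **Missing data.** Same section: "Surveys with more than 50% missing responses will not be included in the data analysis". Then: "There will be no missing data imputation, and the analysis of the included survey responses and results will be based on completed survey data".
- **Expected response.** Sample Size Estimation sets enrolment "Based on the maximum survey completion rate attained for the Text4Hope and Text4Mood programs in Alberta of 20" per cent. Limitations adds that response to such surveys is usually below that figure.
- **Dropout.** Participants' Recruitment and Subscription: "the anticipated dropout rate for the email messaging program will be less than 15" per cent. This follows the sentence on unsubscribing, so it concerns leaving the programme and not survey non-response.

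The article states no repeated-measures model and no sensitivity analysis for missing surveys. It gives no follow-up completion rate among those who completed baseline.

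**The concern.** A paired t test can use a teacher only if both surveys of the contrast are present. With five waves and response of 20% or less at each, many teachers may answer one survey of a pair and not the other, and those surveys then contribute nothing to the estimated change. The loss has two parts. Precision is lower than the collected data allow. The estimate is also unbiased only if answering both surveys is unrelated to the scores. The main claim of the study is a before-after change (a reduction of at least 20%, under Hypothesis), so both parts bear on the primary conclusion. The article has fixed the test and the missing-data rule, so this is a choice that can be judged and not a detail left to another document.

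**Working it through.** **Plan's own figures.** 993 / 0.20 = 4965, so enrolment reproduces from the completion rate. The 993 itself does not follow from the stated population of 30,561: 1.96² × 0.25 / 0.03² = 1067, and with the finite-population correction 1032. It matches the Lusaka teachers alone (10,822 + 3383 = 14,205, giving 992.6). With 993 of 30,561 the margin is 3.06%, so this slip is small, separate, and does not affect what follows.

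**Number of pairs, baseline to 12 months.** Inputs: 4965 enrolled, 20% completion, 15% dropout (the plan's upper bound).
- Baseline surveys: 4965 × 0.20 = 993. Twelve-month surveys: 4965 × 0.85 × 0.20 = 844.
- Independent responding: 4965 × 0.85 × 0.20 × 0.20 = 169 pairs, with 993 − 169 = 824 baseline-only and 844 − 169 = 675 follow-up-only surveys.
- Same responders throughout: 844 pairs, 149 baseline-only, none follow-up-only.

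The article does not say where in this range the study will fall.

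**Precision.** Unit variance at each wave, correlation ρ = 0.6 (assumed), m pairs.
- Paired test: variance 2(1 − ρ)/m.
- Independent responding, m = 169: paired 0.8/169 = 0.00473. Unpaired surveys 1/824 + 1/675 = 0.00270. Combined by inverse variance: 0.00172. SE ratio √(0.00172/0.00473) = 0.60, a cut of about 40%.
- Same marginal counts with more overlap: a cut of about 17% at 422 pairs and 9% at 600 pairs (two-wave generalised least squares).
- Only baseline completers answer later: the likelihood estimate has variance (1 − ρ²)/m + (1 − ρ)²/993. At m = 169 this is 0.64/169 + 0.16/993 = 0.00395, SE ratio √(0.00395/0.00473) = 0.91, a cut of about 9%. At m = 844 it is 0.000919 against 0.8/844 = 0.000948, a cut of about 2%.

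**Bias when response depends on the baseline score.** Assumptions: no true change, ρ = 0.6, 35% prevalence, 25% follow-up response among baseline completers, response odds multiplied by 0.8 or 0.7 per SD of a higher symptom score.
- In simulation, responders' mean baseline is then 0.17 or 0.26 SD below that of all baseline completers.
- The expected paired change is (1 − ρ) times that shift: 0.4 × 0.17 = 0.07 SD and 0.4 × 0.26 = 0.10 SD upward, or about 2 to 4 prevalence points. At 20% response the upper value is 0.11 SD.
- The direction is an apparent worsening, because responders start low and regress upward. If worse-off teachers respond more, the sign reverses.
- The likelihood estimate, which uses all baseline surveys, has bias of about 0.

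**Bias when response depends on the unseen follow-up score.** Same assumptions, with the odds ratio now applied to the follow-up score.
- Paired: −(1 − ρ) × shift = −0.07 to −0.10 SD.
- Likelihood: about −(1 − ρ²) × shift = −0.64 × 0.17 to −0.64 × 0.26 = −0.11 to −0.17 SD.

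Here the model is about 1 + ρ = 1.6 times as biased as the paired test.

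**The case against.** Several stronger readings are tempting, and the document does not support them.

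- **That most collected data are discarded.** This depends on a follow-up rate that the article does not give, and with stable responders 844 of the 993 baseline surveys would be paired. Surveys without a partner are left out of the paired tests only. They still enter the baseline prevalence, the correlate models, and the comparison of six-week subscribers with new subscribers.
- **That missing data are not handled at all.** A rule is stated: drop surveys more than half empty, then analyse completed data. It is a complete-case rule, and that is the point at issue.
- **That half-answered scales would be summed as they stand and fall below their cut-offs.** No scoring rule is given, so this is supposition. Completed data may well mean complete items for each analysis, and item scoring is commonly left to a fuller document.
- **That selective response would mimic improvement, and that a mixed model would put this right.** A spurious fall arises when worse-off teachers skip the follow-up because of their follow-up score. A missing-at-random model does not correct that case and can do worse, as shown above. The bias that the model does remove runs the other way when worse-off teachers respond less.

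It is also fair that Limitations admits low response. It links it to a sample shortfall, and discusses generalisability through demographics. It does not mention bias in the change estimates. What survives is narrower than these readings but sound: the stated test uses less of the data than it could, and it carries a correctable bias.

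**Conclusion.** The point holds in this limited form and is worth changing before analysis. Paired t tests on completed surveys are an inferior choice for the change outcomes of a five-wave survey with expected response of 20% or less. The precision gain from modelling all surveys lies between about 2% and 40% of the standard error, with no single figure defensible. It is at most about 9% if only baseline completers answer later. The correctable bias is 0.07 to 0.10 SD, or 2 to 4 prevalence points, under the assumed response odds ratios. These sizes rest on a correlation of 0.6, on 35% prevalence and 25% follow-up response for the bias figures, and on applying the plan's 20% and 15% to the 12-month wave. A mixed model does not protect against response that depends on the follow-up score, and it does not recover teachers who never answer a survey.

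**What to change.** 1. Replace the paired t tests with a linear mixed model for the scale scores. For the prevalence outcomes, which make up most of the primary outcomes, use a mixed logistic model or a response-weighted GEE. Enter every available survey, with time as a factor.
2. At each wave, compare baseline scores of follow-up responders and non-responders, and report the number of pairs.
3. Add a not-at-random sensitivity analysis, for example a delta shift applied to the unobserved follow-up scores over a stated range.

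The cost is a little more analysis work and reliance on the missing-at-random assumption for the main estimate, which step 3 is there to test. No extra data are needed.

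### Twenty-four primary comparisons share one unadjusted two-sided .05 threshold with no main time point, so the chance of a false effectiveness finding is well above the nominal level

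*Protocol article*

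**What the plan says.** Outcomes and Measures defines the primary set: "Primary outcomes for this study will be changes in mental health literacy and the prevalence of moderate to high stress, burnout, moderate to high anxiety", continuing to depression and "low resilience from baseline to 6 weeks, 3 months, 6 months, and 12 months among the subscribers". That is six outcomes at four follow-ups, none marked as the main one. Changes in mean score on the five symptom, burnout and resilience scales are listed there as secondary.

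Statistical Analysis sets one threshold for everything, a two-tailed P≤.05 that "will be used to determine statistical significance for all analyses". For programme impact it lists five constructs ("reducing moderate to high anxiety, moderate to high depression, moderate to high stress, burnout, and improving resilience among subscribers will be evaluated") and one method: "comparing the mean changes in these parameters from baseline to 6 weeks, 3 months to 6 months, and 12 months using the paired *t* test". It then adds a 6-week comparison of established with new subscribers on prevalence and mean scores for stress, anxiety, burnout and depression.

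Study Objectives and Hypothesis both anticipate a reduction of at least 20% in the prevalence and severity of the five conditions. Hypothesis adds at least a 20% improvement in literacy. Neither says how many of these must be met, or at which follow-up.

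**The concern.** The article intends a confirmatory conclusion. Its Discussion and Conclusions expect the results to establish effectiveness and to inform school policy and resource allocation. With 24 unranked primary comparisons at a common .05, the plan does not separate a success specified in advance from the best of 24 results. The .05 is the error rate of one test, not of the statement that the programme works.

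This is more than silence that an analysis plan could fill. The article fixes both the primary set and the threshold for all analyses, so a hierarchy or adjusted threshold introduced later would have to change what is stated here.

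**Working it through.** **Inputs from the article.** Six primary outcomes and four follow-ups (Outcomes and Measures); two-sided .05 for all analyses (Statistical Analysis), which is .025 per test in the direction of benefit. The article gives no power or error-rate figure for the primary changes to reproduce. Its sample size of 993 is a precision target for baseline prevalence and does not enter here.

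**Assumed.** Correlations among outcomes and among follow-ups are not given. The Introduction says only that stress, burnout, anxiety and depression overlap, so a range is shown.

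**Number of comparisons.** 6 × 4 = 24.

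**Independent tests, no effect.**
- Any significant result, either direction: 1 − 0.95^24 = 0.708.
- Any significant result in the direction of benefit: 1 − 0.975^24 = 0.455.
- Expected number of false positives: 24 × 0.05 = 1.2, half of them (0.6) in the direction of benefit.

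**Correlated tests, no effect.** Multivariate normal test statistics, critical value 1.96. The first three rows use a separate correlation between outcomes and between follow-ups, multiplied when both differ. The last two use one common correlation for all pairs.

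| Correlation | Any direction | Benefit |
|---|---|---|
| 0.5 outcomes, 0.5 follow-ups | 0.53 | 0.28 |
| 0.5 outcomes, 0.7 follow-ups | 0.46 | 0.24 |
| 0.7 outcomes, 0.7 follow-ups | 0.38 | 0.19 |
| 0.5, all pairs | 0.46 | 0.23 |
| 0.7, all pairs | 0.31 | 0.16 |

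Over this range the chance is 31–53% in either direction and 16–28% for benefit. Against 5% and 2.5% that is about 6 to 11 times nominal (0.31/0.05 = 6.2; 0.28/0.025 = 11.2). At an extreme 0.9 for both correlations it is still 19% and 10%.

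**Sensitivity to the count.** With only the five constructs named for the paired t test, at four follow-ups, there are 20 tests. Independent tests then give 1 − 0.95^20 = 0.64 and 1 − 0.975^20 = 0.40.

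**Which part of the multiplicity matters.**
- One outcome at four unranked follow-ups: 1 − 0.95^4 = 0.19 if independent, 0.16 at correlation 0.5, 0.13 at 0.7.
- Six outcomes at one follow-up: 1 − 0.95^6 = 0.26 if independent, 0.21 at 0.5, 0.16 at 0.7.

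Naming a time point alone is therefore not enough for a claim about the programme as a whole.

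**After the fix.** The first Holm step for six outcomes is 0.05/6 = 0.0083. With no effect on any outcome, the familywise error is 1 − (1 − 0.0083)^6 = 0.049 if independent. Holm keeps it at or below .05 under any correlation.

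**The case against.** **The size is easy to overstate.** A reader might infer from the 71% that a false claim of benefit is likely. The documents do not support that. The 71% counts significant harm as well as benefit and assumes independence, the least plausible case for overlapping conditions measured repeatedly in the same people. False benefit stays below one half over the 24 primary comparisons even if they are independent.

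**The 24 comparisons are not 24 specified tests.** A reader might also infer that each primary outcome is tested at each follow-up. Statistical Analysis names within-subscriber tests only for mean changes in five constructs. It omits literacy there, names no within-subscriber test for change in prevalence, and words the intervals differently from the outcome definition. This objection stands as to wording. It does not remove the problem, because the 24 changes are defined as primary and the threshold covers all analyses.

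**There is a success target.** The 20% hypotheses are worded jointly, and if success required every outcome at a given time point, no adjustment across those outcomes would be needed. But they are targets rather than a decision rule, and they leave the time point open. Equally, the article nowhere says that a single significant result would suffice, so that too is only a possible reading.

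**Multiplicity often belongs in the analysis plan, and adjusted p-values could be compared with .05.** That is possible, but nothing in the article indicates it, and the unranked primary set is a protocol matter.

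**Adjustment does not cure a before-after design.** This is correct. The calculation concerns chance error only.

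**Conclusion.** The point holds in this form: 24 comparisons are defined as primary, none is ranked, and one two-sided .05 applies throughout with no hierarchy, adjustment or success rule. With no effect, the chance of at least one significant primary result is up to about 71% in either direction and up to about 46% for benefit. It is about 31–53% and 16–28% at correlations of 0.5 to 0.7. The upper figures assume independence. The lower ones rest on correlations that the article does not give. All of them count the comparisons that Outcomes and Measures defines, and none includes bias from the uncontrolled before-after comparison. The design need not change, but the stated .05 is not the error rate of an effectiveness claim, so the plan should be corrected before results are seen.

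**What to change.** 1. Name 12 months, which the abstract calls the end point, as the single primary time point.
2. Apply Holm's procedure there across the six primary outcomes at overall two-sided .05. The smallest p-value is compared with .0083, the next with .05/5 = .01, and so on. The tests should be paired tests of the outcomes as Outcomes and Measures defines them: change in prevalence for the five conditions (for example McNemar's test) and change in score for literacy.
3. Report 6 weeks, 3 months and 6 months as secondary, with confidence intervals and no confirmatory claim. The mean-score changes on the five scales are already secondary and stay so.
4. If the 6-week comparison with new subscribers is also to carry a claim, make it a separate family limited to stress, anxiety, burnout and depression, with its own Holm adjustment (first step .05/4 = .0125). It cannot carry the six-outcome family, because it does not cover literacy or resilience.

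This takes a short paragraph and no new data. It also requires the paired tests for prevalence and literacy to be named, which the impact analysis does not yet do. The downside is a stricter threshold for individual outcomes.
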